#### Empathy of VIPP-V intervention worker

Empathy of the VIPP-V intervention worker can be expected to be associated with the relationship between the VIPP-V intervention worker and the parent [41] and may therefore, contribute to the effectiveness of intervention. To assess empathy of the VIPP-V intervention workers the short version of the **Empathy Quotient (EQ-short)** [42, 43] is used at pretest and post-test. This questionnaire consists of 22 items which measure how easily one picks up other people’s feelings and how strongly one is affected by those feelings. Items are scored on a 4-point scale, ranging from *“totally disagree (1)”* to *“totally agree (4).”* An example of an item is: *“I can easily tell if someone else wants to enter a conversation.”* The short version of the EQ-short has been shown to have good validity and reliability (Cronbach’s alpha = 0.90) [43].

### Measures of control variables

Potential stressful experiences during intervention and treatment integrity will be measured and used as control variables.

#### Potential stressful experiences

To control for the effect of stressful experiences in the child’s life on the effectiveness of the VIPP-V intervention, the VIPP-V intervention worker is asked to check any potential stressful experiences in the child’s life on a checklist at pretest and post-test.

#### Treatment integrity

All home-visits are video-taped to provide video-feedback. These video-tapes will also be used to assess whether the intervention is carried out according to the manual. Ten percent of the video-tapes will be randomly selected to code treatment integrity.

### Procedure

To recruit families for participation in the study Royal Dutch Visio and Bartiméus will send an information package, including a letter, brochure and consent form developed by the researchers, as well as a cover letter from the organization to all families in their databases who meet the inclusion criteria. In addition to this broad approach, also all early intervention workers are asked to personally inform the families in their caseload who are eligible for participation about the study. If families decide to participate in the study, they sign a consent form and fill out a demographic questionnaire. When they return these forms to the university, their personal data becomes known to the researchers. Families who are approached for participation, but do not wish to participate in the study, remain anonymous to the researchers. If parents have questions regarding the study they can phone or email one of the eight VIPP-V coaches working at Royal Dutch Visio and Bartiméus or one of the researchers.

After informed consent and demographics are obtained, families are enrolled in a block of 16–18 families. In both organizations three blocks of 16–18 families will be formed, to include a total of 100 families in the study. When the maximum number of families for the block is reached, families will be randomized, and a few weeks later the intervention will start. The intervention will start on three different occasions over the year, so each intervention worker provides VIPP-V to approximately one family at a time. After randomization families are informed in which condition they will participate through a letter by the research team. A research assistant makes an appointment with the family for the pretest assessment (T1). After the pretest the intervention starts. After about five months the intervention is finished and a post-test takes place. Three months later an appointment is made for the follow-up assessment. Families participating in the control condition will be assessed at the same time points (see Fig. 1).

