**Methods/Design:**

A randomized controlled trial (RCT) will be conducted to assess the effectiveness of the adapted intervention VIPP-V (Video-feedback Intervention to promote Positive Parenting in parents of children with Visual or visual-and-intellectual disabilities). Parent-child dyads will be randomized into two groups: 50 dyads will receive VIPP-V in combination with care-as-usual and 50 dyads will receive care-as-usual. Families with a child (1–5 years of age) with a visual or visual-and-intellectual disability will be recruited for participation in the study. Primary outcome measures are parental sensitivity and the quality of parent-child interaction. Secondary outcome measures are parental self-efficacy, and parenting stress. To assess feasibility of implementation of the intervention the experiences of early intervention workers with regard to using VIPP-V are assessed. Moderator variables are the child’s developmental age, working alliance between parent and VIPP-V intervention worker and empathy of the VIPP-V intervention worker. Data will be collected approximately one week before the intervention starts (T1), one week (T2) and three months (T3) after the intervention. Parent-child dyads in the care-as-usual-only condition will be assessed at the same time points. Both intention-to-treat and completer analyses will be performed.

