### Randomization

Randomization will be done by use of a computerized random number generator by the first author. Using stratified randomization, equal randomization of families from both Royal Dutch Visio and Bartiméus will be achieved, as well as equal representation of children with varying chronological ages. Stratified randomization reduces the risk for baseline imbalance between conditions [44]. For each organization separately, the random allocation list will be generated in three blocks with a 1:1 allocation, based on three periods in which the intervention will be offered. After the second block a check will be done for baseline imbalances between conditions, so, if necessary, these imbalances can be corrected in the final block. Each block will be randomized roughly three weeks before the start of the intervention. The numbers on the list will be paired with the participating families in order of the date on which informed consent is obtained.

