### Blinding

Parents agree to participate in the study before randomization and without knowing in which condition they will participate. The condition in which parents will participate will be disclosed to them directly after randomization of the block they belong to (roughly three weeks before the start of the intervention). Every ID-number assigned to families is independent of condition. Researchers coding and analyzing the observation data will be blind to the condition of parents and children, as well as the assessment (pretest, post-test, follow-up). Research assistants conducting the assessments are not blinded to the condition or assessment, because different questionnaires are used for families participating in the intervention condition and in the control condition (families in the control condition are not asked about working alliance of the VIPP-V intervention worker) and per assessment. Intervention workers are, necessarily, not blind to randomization allocation.

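### T1 is measured about two weeks after families learn their allocation, so the baseline for the change analyses is post-randomisation and comes from parents who know their arm

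*Protocol article*

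**What the plan says.** Four places in the protocol article fix the order of events.

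- **Procedure.** Consent and the demographic questionnaire come first, and families are then gathered into a block that is randomised once full. Next: "After randomization families are informed in which condition they will participate through a letter by the research team". Then: "A research assistant makes an appointment with the family for the pretest assessment (T1). After the pretest the intervention starts". Controls are assessed at the same time points.
- **Randomization.** "Each block will be randomized roughly three weeks before the start of the intervention".
- **Blinding.** The parents' condition "will be disclosed to them directly after randomization of the block they belong to". The research assistants who run the assessments know both condition and time point. Those who code and analyse the observation data know neither.
- **Abstract, Methods/Design.** "Data will be collected approximately one week before the intervention starts (T1), one week (T2) and three months (T3) after the intervention".

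T1 then carries much of the inference. Both hypotheses are worded as stronger improvement, increase or decrease. The powered test is the condition-by-assessment interaction with pretest as one of three levels (Sample size calculation). Data analysis assesses change from pretest to post-test and to follow-up, and also compares the arms at the same assessment. Under Drop-outs, families are followed from pretest onward and missing assessments are filled with the last value.

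**The concern.** A baseline should be out of reach of the allocation. Here parents fill in the self-efficacy (SENR) and stress (PSI) questionnaires, and are filmed at play, already knowing whether they will receive the intervention. They had agreed to a study for which willingness to take part in video-feedback was an eligibility condition. Disappointment in one arm or anticipation in the other could therefore move T1. A T1 shift in one arm that later fades appears in a change analysis as an effect of opposite sign, and adjusting for the shifted T1 does not fully remove it.

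There is a second route. A family that leaves between the letter and T1 has no outcome value, so last value carried forward has nothing to carry. The planned intention-to-treat analysis cannot cover the interval in which learning the allocation might prompt withdrawal, and such loss may differ by arm.

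**Working it through.** **1. The plan's own figure.** Power for the interaction, from the noncentral F distribution, with f = 0.17, two arms, three assessments and alpha 0.05. The correlation between assessments is not stated; 0.5 and sphericity are assumed.

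λ = f² × N × 3 / (1 − ρ)

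- N = 100: λ = 0.0289 × 300 / 0.5 = 17.34, df 2 and 196, power 0.967 (stated 0.97).
- N = 58: λ = 0.0289 × 174 / 0.5 = 10.06, df 2 and 112, power 0.807 (stated 0.80).

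Both figures reproduce. Neither depends on when T1 is taken, so the point concerns bias and not sample size.

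**2. Interval.** Disclosure about 3 weeks before start, minus T1 about 1 week before start, gives about 2 weeks of knowing the arm. Both inputs are approximate in the text; the order is not.

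**3. Who knows the arm at T1.**

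| Outcome | Parent | Research assistant | Scorer |
|---|---|---|---|
| SENR, PSI (secondary) | knows | knows | parent's own report |
| Video-coded interaction (primary) | knows | knows | blind to condition and time point |

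**4. Size under an assumed shift.** The documents give no figure for a reaction to the letter. Let b be the T1 difference between arms that it causes, in SD, and p the fraction still present at T2. Errors are measured against the effect free of any such reaction.

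- Change from T1: p·b − b = −(1 − p)·b
- Adjusted for T1 with correlation ρ: p·b − ρ·b = (p − ρ)·b
- Arms compared at T2 only: p·b

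With ρ = 0.5 (assumed):

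| p | Change | Baseline-adjusted | T2 only |
|---|---|---|---|
| 0 (fades) | −b | −0.5b | 0 |
| 0.5 | −0.5b | 0 | 0.5b |
| 1 (persists) | 0 | 0.5b | b |

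For b of 0.1-0.2 SD in either direction, the error in the change contrast is between 0 and 0.1-0.2 SD. The upper end is 0.1/0.33 = 30% to 0.2/0.33 = 61% of the expected effect. Half fading gives 0.05-0.10 SD (15-30%). With baseline adjustment the largest error is 0.05-0.10 SD. Under full fading, a true 0.33 would be estimated as 0.33 − 0.2 = 0.13 when b = +0.2, and as 0.33 + 0.2 = 0.53 when b = −0.2.

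**5. False-positive rate at the full-fade end.** With 50 per arm, ρ = 0.5 and no true effect, the standard error of the change contrast is √(2 × 0.5) × √(2/50) = 0.20 SD. The two-sided 5% test then rejects in 7.9% of trials at a shift of 0.1 SD and 17% at 0.2 SD. Baseline-adjusted (standard error √0.75 × 0.20 = 0.173, error 0.5b), the rates are 6.0% and 8.9%.

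**The case against.** The strongest reply is that the primary outcome is protected. Tapes are scored by coders blind to condition and assessment, so a reader who infers that the whole baseline is unblinded goes too far. This stands. For the primary outcome the letter would have to change what parents do in a play task of about 15 minutes, or change who reaches T1.

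Second, T1 is not the only reference. Data analysis also compares the arms at the same assessment, and the main research question under Primary outcome measures is put as a comparison with care-as-usual. This also stands, although the hypotheses and the powered test do involve T1.

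Third, a reader might infer that withdrawal before T1 is selective by arm. The documents do not show that; it is only possible. Demographics are collected before randomisation and reasons for drop-out are to be documented, so early leavers can be counted and described by arm, though they still have no outcome value.

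Fourth, disclosure first might seem to be needed because the forms differ by arm. The Blinding section gives that reason for unblinded assistants, but the only arm-specific parent form it names, working alliance, is given at post-test. The intervention worker does complete an empathy questionnaire and a checklist of stressful experiences at pretest, so a worker may already be linked to a family by then. That does not require the parent to know.

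Fifth, data collection is in progress (Status of the trial), and the document does not show that any block remains to be randomised. This limits what can still be changed.

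**Conclusion.** The point holds as a design weakness. Randomisation, disclosure and then T1 is the explicit order, and it exposes the baseline used in the change analyses to knowledge of the arm. Exposure is direct for self-efficacy and parenting stress, and indirect for the primary outcome. Loss between letter and T1 falls outside the carry-forward rule.

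Neither size nor direction can be read from the documents. The 30-61% is the extreme of a range that begins at 0. It rests on an assumed shift of 0.1-0.2 SD that has fully faded by T2, and should not be quoted as the expected bias, least of all for the blind-coded outcome. The halved figure for baseline adjustment rests further on an assumed correlation of 0.5. The documents do not support a reading that the trial's conclusions are invalid. They support closing an avoidable route of bias where that is still possible, and reporting openly where it is not.

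**What to change.** **Any block not yet randomised.** Complete T1 for the block before it is randomised. At minimum, hold each family's allocation letter until its T1 visit is done, preferably with the assistant also unaware of the arm at that visit. The worker-completed pretest forms can follow allocation.

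**Blocks already run.** Report the number of families lost between letter and T1 by arm, with their demographics. State as a limitation that T1 followed disclosure. Give the between-arm T2 and T3 comparisons, which do not rest on T1, alongside the change analyses. With 50 per arm, the T2 comparison has a standard error of √(2/50) = 0.20 SD, the same as the change contrast at a correlation of 0.5. The two sets err in different circumstances (step 4 of the working), so agreement between them is informative. Neither removes a reaction that lasts to T2, which would be present even with an earlier T1.

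**Cost.** Sample size and power are unchanged. Families hear their allocation later, or T1 lies somewhat further from the start. Home visits to 16-18 families per block in each organisation must fit in before allocation or before the letters go out. Ethical considerations requires changes to the study procedures to go to the ethics committee as amendments. Baselines would differ in timing between early and late blocks, which should be stated in the report.

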**Fig. 1 Fig1:**
[figure not shown]
Research procedure. EQ-short = Empathy Quotient short questionnaire; PSI = Parenting Stress Index; SENR = Self-efficacy in the Nurturing Role questionnaire; VABS = Vineland Adaptive Behavior Scales; VIPP-V = Video-feedback Intervention to promote Positive Parenting in parents of children with Visual or visual-and-intellectual disabilities; WAI = Working Alliance Inventory

Assessments take place in the home of the family and consist of a computerized administration of questionnaires for the parent, which takes about 20–30 minutes, and a parent-child interaction play task of about 15 minutes (see Measures for a more extensive description of the study instruments). After each assessment parents receive a small gift (for example a puzzle, stuffed animal or book) for their child. During the study, participating families will be informed about the study progress through a newsletter. At the end of the study, all families will receive a general report on the effect of VIPP-V. This procedure was approved by the Medical Ethics Committee (METc VUmc 2013/449/NL47334.029.13).

### Randomization

Randomization will be done by use of a computerized random number generator by the first author. Using stratified randomization, equal randomization of families from both Royal Dutch Visio and Bartiméus will be achieved, as well as equal representation of children with varying chronological ages. Stratified randomization reduces the risk for baseline imbalance between conditions [44]. For each organization separately, the random allocation list will be generated in three blocks with a 1:1 allocation, based on three periods in which the intervention will be offered. After the second block a check will be done for baseline imbalances between conditions, so, if necessary, these imbalances can be corrected in the final block. Each block will be randomized roughly three weeks before the start of the intervention. The numbers on the list will be paired with the participating families in order of the date on which informed consent is obtained.

### Blinding

Parents agree to participate in the study before randomization and without knowing in which condition they will participate. The condition in which parents will participate will be disclosed to them directly after randomization of the block they belong to (roughly three weeks before the start of the intervention). Every ID-number assigned to families is independent of condition. Researchers coding and analyzing the observation data will be blind to the condition of parents and children, as well as the assessment (pretest, post-test, follow-up). Research assistants conducting the assessments are not blinded to the condition or assessment, because different questionnaires are used for families participating in the intervention condition and in the control condition (families in the control condition are not asked about working alliance of the VIPP-V intervention worker) and per assessment. Intervention workers are, necessarily, not blind to randomization allocation.

### Sample size calculation

The total sample size is based on an expected effect size of *d* = 0.33 (*f* = 0.17), based on a meta-analysis on RCTs of interventions focusing on improving maternal sensitivity [15]. Based on an alpha of 0.05 and a sample of 100 families, adequate statistical power will be achieved (0.97) for testing the significance of an interaction effect between the between-subject factor (experimental versus control condition) and the within-subject factor (assessment: pretest, post-test, follow-up) in repeated measures analysis of variance (ANOVA) using the full sample of 100 families. If, due to circumstances such as drop-out, illness of VIPP-V intervention workers or unexpected organizational aspects, the number of families drops, with an effect size this high, high power (0.80) can still be achieved with 58 families for the main research question regarding effectiveness of intervention on parental sensitivity. However, to also perform moderator analyses with adequate power we aim to include 100 families in the study.

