## Methods

### Study design

This study is a multicenter RCT with pretest, post-test assessments and follow-up after three months (three time points), including two groups: an experimental group who will receive VIPP-V in combination with care-as-usual, and a control group who will only receive care-as-usual. Randomization will be performed as stratified block randomization with a 1:1 allocation. This trial will be carried out in two national organizations specialized in care for people with visual disabilities and their families (Royal Dutch Visio and Bartiméus). These organizations have offered services to people with visual disabilities and their families since the 1980s and have multiple rehabilitation centers all over The Netherlands. Together, Royal Dutch Visio and Bartiméus provide care for the majority of families eligible for participation in the study (with the exception of families living in the three northern-most counties because of organizational issues).

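### The stated power of 0.97 (100 families) and 0.80 (58 families) treats f = d/2 as the group-by-time interaction effect; at d = 0.33, held at T2 and T3, with an assumed within-person correlation of 0.5, the stated test has about 0.38 and 0.23

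*Protocol article*

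**What the plan says.** The section Sample size calculation starts from an "expected effect size of *d* = 0.33 (*f* = 0.17), based on a meta-analysis on RCTs of interventions focusing on improving maternal sensitivity". The powered test is the interaction of condition (two levels) with assessment (pretest, post-test, follow-up) in a repeated measures ANOVA. For that test it states: "Based on an alpha of 0.05 and a sample of 100 families, adequate statistical power will be achieved (0.97) for testing the significance". It then says that if the number of families drops, "high power (0.80) can still be achieved with 58 families for the main research question regarding effectiveness of intervention on parental sensitivity", and in the same sentence describes the effect size as high. The target of 100 is kept so that moderator analyses also have adequate power.

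The Study design section confirms three time points and 1:1 allocation. The article states neither a correlation between assessments nor a pattern of group differences over time.

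**The concern.** An f of 0.17 is d/2 after rounding (0.33/2 = 0.165). That identity holds for one comparison of two independent means. The f of a group-by-time interaction is a different quantity: it measures how much the group difference varies across the assessments. Randomised groups are expected to be equal at pretest, so a later difference of d produces an interaction f well below d/2.

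If d/2 was used as the interaction effect, the calculation powers the trial for a group difference more than twice the one the sponsor expects. Two statements then fail: that 100 families give near-certain detection of d = 0.33, and that the main question stays well powered after a loss of 42 of the 100 families. A reader of the eventual results who relied on 0.97 would also give a non-significant interaction more weight than it deserves.

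**Working it through.** **Inputs from the article.** d = 0.33, f = 0.17, alpha 0.05, N = 100 and N = 58, two groups, three assessments, 1:1 allocation.

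**Assumptions, not in the article.** Within-person correlation ρ, equal for all pairs of assessments (sphericity); independent families; the pattern of group differences over time.

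**Formula.** For the interaction in a 2 × 3 repeated measures ANOVA, power comes from the noncentral F distribution with df₁ = 2, df₂ = 2(N − 2) and λ = 3N f²/(1 − ρ).

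**Step 1: reproduce the stated figures.** Take f = 0.17 and ρ = 0.5.
- N = 100: λ = 300 × 0.0289/0.5 = 17.34, power 0.967.
- N = 58: λ = 174 × 0.0289/0.5 = 10.06, power 0.807. N = 56 gives 0.792, so 58 is the smallest even N that reaches 0.80.

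With f = 0.17, other correlations miss both figures: ρ = 0.3 gives 0.888 and 0.655; ρ = 0.6 gives 0.990 and 0.890.

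**Step 2: derive the interaction f from d.** Let the group differences at T1, T2, T3 be (0, d, d), with mean 2d/3. Halve the deviations from that mean, since each group lies half the difference from the midpoint: (−d/3, d/6, d/6). The mean square is (d²/9 + d²/36 + d²/36)/3 = d²/18, so f = d/√18. At d = 0.33, f = 0.078. Conversely, f = 0.17 requires d = 0.17 × √18 = 0.72 at both T2 and T3.

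**Step 3: power at d = 0.33.** f² = 0.1089/18 = 0.00605. At ρ = 0.5:
- N = 100: λ = 300 × 0.00605/0.5 = 3.63, power 0.376.
- N = 58: λ = 174 × 0.00605/0.5 = 2.11, power 0.230.

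A simulation of the ANOVA with 20,000 trials per N gave 0.380 and 0.228.

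**Step 4: vary the unstated inputs.**

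| Pattern (T1, T2, T3) | ρ | Power, N = 100 | Power, N = 58 |
|---|---|---|---|
| (0, d, d) | 0.3 | 0.28 | 0.18 |
| (0, d, d) | 0.5 | 0.38 | 0.23 |
| (0, d, d) | 0.7 | 0.58 | 0.36 |
| (0, d, d) | 0.8 | 0.77 | 0.51 |
| (0, d, d) | 0.9 | 0.97 | 0.83 |
| (0, d/2, d) or (0, d, d/2) | 0.5 | 0.29 | 0.18 |
| (0, d, 0) | 0.5 | 0.38 | 0.23 |
| (0, d, 1.5d) | 0.5 | 0.60 | 0.38 |

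If d is standardised on the pretest-to-later change score instead, power for (0, d, d) at N = 100 is 0.376 whatever ρ is.

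**Step 5: detectable effect.** For (0, d, d) and ρ = 0.5, 80% power needs d of about 0.54 with 100 families and about 0.72 with 58.

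**The case against.** The strongest reply is that 0.38 is no more a fact of the document than 0.97, because it depends on a correlation and an effect pattern that the article does not give. That stands, so the figure must carry its assumptions. It does not rescue 0.97, which no correlation from 0.3 to 0.8 reaches under (0, d, d). An effect that grows to 1.5d by follow-up reaches only 0.60 at ρ = 0.5.

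A second reply is that the origin of the stated figures is inferred. Power depends on f and ρ only through f²/(1 − ρ), so f = 0.078 with ρ of about 0.895 also gives 0.967 and about 0.805. It would be too strong to say that the error is the only route to the stated numbers. But the article prints f = 0.17, and a correlation near 0.9 across eight months is hard to credit when the intercoder reliability it cites is 0.83 to 0.87.

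A third reply is that the Data analysis section also plans pretest-to-post-test and pretest-to-follow-up comparisons and allows multilevel models, so the omnibus test is not the whole analysis. True, but the stated power is for the omnibus interaction. A single contrast of the T2/T3 mean against T1, which the article does not name, would have about 0.47 at ρ = 0.5.

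Finally, a reader might infer that the sponsor would stop at 58 families, or would read a null result as evidence against the intervention. The article says neither. It aims for 100 throughout, and 58 is a reassurance, not a threshold. The reassurance is still wrong.

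**Conclusion.** The stated power is wrong as written for the effect the plan expects. Under (0, d, d), ρ = 0.5, sphericity and no clustering by intervention worker, the planned interaction test at d = 0.33 has power of about 0.38 with 100 families and 0.23 with 58, against 0.97 and 0.80 stated. For ρ from 0.3 to 0.8 the ranges are 0.28 to 0.77 and 0.18 to 0.51. The exact values are conditional; the overstatement holds across the whole range.

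Two stronger readings are tempting and should not be adopted. One is that a null result is more likely than not at d = 0.33. That holds at ρ = 0.5 but not at 0.7 or 0.8, where power is 0.58 and 0.77. The other is that a non-significant result cannot exclude d = 0.33. As a general rule that is false: a post-test estimate of −0.10 with a standard error of √(2/50) = 0.20 has an upper 95% limit of −0.10 + 1.96 × 0.20 = 0.29, below 0.33. The confidence interval decides, not the test alone.

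**What to change.** Keep the target of 100 families and reword the sample size paragraph:

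- Give power for d = 0.33 under the stated interaction test, with the assumed correlation and effect pattern: about 0.38 with 100 families at ρ = 0.5 for (0, d, d), with the range 0.28 to 0.77 for ρ from 0.3 to 0.8, and 0.29 for a gradual effect. If the smaller sample is still discussed, give its 0.23, range 0.18 to 0.51, and 0.18 in the same way.
- Give the detectable d at 80% power for that test: about 0.54 with 100 families and 0.72 with 58, at ρ = 0.5.
- Delete the claim that 58 families give 0.80, and the remark that the effect size is high.
- State that a non-significant interaction test does not by itself exclude d = 0.33, and that the confidence interval for the group difference will be reported.

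The cost is one reworded paragraph and a visibly less favourable power statement. No extra families are needed, and the conduct of the trial does not change.
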